### Statistical analysis

#### Sample size

In this trial, according to the previous study [18], the total dose of propofol in the dream group was 337 ± 161 mg and by 259 ± 145 mg in the no dream group. Using a *t* test of two independent samples in PASS for calculation, the withdrawal rate is 20% to ensure that the results are statistically different (*α* = 0.05, 1-*β* = 0.8); therefore, each group requires 56 subjects. To improve the reliability of the trial, we will recruit a total of 124 patients, with 62 in each group.

The SPSS 20.0 statistical software (SPSS, Inc., Chicago, IL, USA) and GraphPad Prism 6.0 software were used for data analysis. Continuous data were tested for normality. Normally distributed data were summarized using mean and standard deviation and were compared using unpaired two-tailed *t*-tests. Skewed data were summarized using.median and range and were compared using Wilcoxon rank-sum tests. Categorical data were summarized using number (%) and were compared using *Χ*^2^ test or Fisher’sexact tests. Logistic regression was used to determine predictors of dreaming and correlation with dream quality. Categorical variables were created from continuous variables in applicable cases. A *P* value of less than 0.05 was considered statistically significant.

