#### Methods in analysis to handle protocol non-adherence and any statistical methods to handle missing data {20c}

All researchers will be trained referring to the same training protocol. Missing intraoperative data, if any, will be obtained from the electronic hospital files. Postoperative evaluation at specified time points is mandatory, and missing postoperative data are not to be anticipated. Analyses of all outcomes will be performed according to the intention-to-treat principle, and once enrolled, all participants will be analyzed, regardless of the findings.

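### The stated 56 per group does not follow from its own inputs: a two-sided t test needs 62 evaluable per group, or 78 after a 20% withdrawal allowance, so the recruited 62 per group contains no margin

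*Protocol article*

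**What the plan says.** All the inputs stand in the Sample size section. From a previous study, "the total dose of propofol in the dream group was 337 ± 161 mg", against "259 ± 145 mg in the no dream group". The method is a t "test of two independent samples in PASS for calculation", with alpha 0.05 and power 0.8. The allowance for loss is worded "the withdrawal rate is 20% to ensure that the results are statistically different". The result is "therefore, each group requires 56 subjects". The section then says that, to make the trial more reliable, "we will recruit a total of 124 patients, with 62 in each group".

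The sample-size sentence does not state sidedness. The analysis paragraph below it does: normally distributed data "were compared using unpaired two-tailed" t-tests.

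The section on non-adherence and missing data (item 20c) makes postoperative evaluation mandatory, says that "missing postoperative data are not to be anticipated", and commits to analysing every enrolled participant by intention to treat.

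**The concern.** A sample size should be reproducible from its stated inputs. Here the difference, both SDs, the test, alpha, power and withdrawal rate are all given, yet the result is smaller than the number needed before any withdrawal is considered.

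A reader of the paragraph would conclude that 56 per group already covers 20% withdrawal and that 62 adds 6 per group of safety. If the requirement is 62 evaluable, there is no safety and the withdrawal allowance is uncovered. The two sections also set different expectations: 20% of 124 is about 25 patients, whereas item 20c expects no missing postoperative data. Which of these applies decides whether the stated power is met.

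**Working it through.** **Inputs (Sample size section).** Means 337 and 259 mg, difference 78 mg; SDs 161 and 145 mg; alpha 0.05; power 0.80; withdrawal 20%; equal groups. Two-sided, from the analysis paragraph.

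**Effect size.** Pooled SD = √((161² + 145²)/2) = √((25,921 + 21,025)/2) = √23,473 = 153.2 mg. Standardised effect = 78/153.2 = 0.509.

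**Attempt to reproduce 56.**

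| Route | Evaluable per group | With 20% withdrawal: n/0.8 | n × 1.2 |
|---|---|---|---|
| Two-sided t, both SDs | 62 | 78 | 75 |
| Two-sided normal approximation, both SDs | 61 | 77 | 74 |
| Two-sided t, SD 161 in both groups | 68 | 85 | 82 |
| Two-sided t, SD 145 in both groups | **56** | 70 | 68 |
| One-sided t, both SDs | 49 | 62 | 59 |

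Of these routes, only one gives 56 exactly: the smaller SD in both groups and no withdrawal allowance. That drops two inputs stated in the same paragraph. It is a possible origin of the figure, not a justification. Some one-sided variants come within two or three of 56, such as SD 145 in both groups (44/0.8 = 55), but they too leave the stated inputs and conflict with the two-tailed analysis.

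**Required number.** The normal approximation is n = 2(1.960 + 0.842)² × 153.2²/78² = 60.6, so 61. With the noncentral t distribution, power is 79.6% at 61 and 80.3% at 62, so 62 evaluable per group are needed. A Welch test also needs 62. Allowing for 20% withdrawal: 62/0.8 = 77.5, so 78 per group, 156 in total.

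**Power at the numbers in the plan (two-sided t, both SDs, equal groups).**

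| Per group | Evaluable | Power |
|---|---|---|
| 56, read as evaluable | 56 | 76.1% |
| 56, read as randomised, 20% lost | 44.8 | about 66% |
| 62, no loss | 62 | 80.3% |
| 62, 20% lost | 49.6 | 70.9% (49: 70.4%; 50: 71.2%) |

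The last two rows describe the actual plan.

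**The case against.** **The 71% is conditional.** A reader might infer that the trial as recruited has only 71% power. The documents do not support that without its condition. Complete data give 80.3%, and there are reasons to expect little loss: patients expected to be unavailable for interview are excluded, the dreaming questionnaire is given as soon as orientation returns, and the sizing variable, total propofol, is an intraoperative record recoverable from hospital files. This stands. It bears on the consequence and leaves 56 unexplained.

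**A larger shortfall.** Reading 56 as the number randomised gives about 66% and a gap of 13 to 14 points. Nobody plans to randomise 56; the Abstract, the randomisation section and the Sample size section all give 124 in total or 62 per group. The range for the plan is 0 to about 9 points.

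**A contradiction between sections.** One might say that 20% withdrawal and no expected missing data cannot both hold. A withdrawal rate can be a planning allowance, and item 20c states an expectation. They are in tension and should be aligned, but they are not logically incompatible.

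**A one-sided calculation.** It gives 49/0.8 = 62, the number recruited. But the text names 56 as the requirement and explains 62 as an addition, and the planned t-tests are two-tailed.

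**What the figures describe.** This is the strongest point. The inputs compare propofol dose between patients who dreamed and those who did not. The 62 v 62 split is by BIS group, and the randomised question is the proportion who dream. A reader might take 80.3% or 71% as the power of the randomised comparison; nothing in the documents shows that. Even for the dose comparison, equal groups need about half the patients to dream. The Discussion cites an incidence of 18% to 49.7%. At 18% of 124 (about 22 v 102) with no loss, the same means and SDs give about 53% power by Welch, or about 57% with the equal-group pooled SD of 153.2. This stands and limits what a corrected paragraph may claim.

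**Conclusion.** The stated requirement is wrong as written. With the document's own difference, SDs, alpha, power and two-tailed test, 62 evaluable per group are needed, or 78 with 20% withdrawal; 56 falls short by 6 and 22 per group respectively. The recruited 62 per group equals the uninflated requirement and is not a margin.

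For the propofol-dose comparison with equal-sized dream and no-dream groups, the plan's power is 80.3% with complete data and about 71% if the assumed 20% are lost. This rests on a two-sided t test and on using both quoted SDs. The figures say nothing about power for the randomised comparison of dreaming between BIS groups.

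**What to change.** In the Sample size section:

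- Replace 56 with 62 evaluable per group, or 78 per group with a 20% withdrawal allowance, and state that the test is two-sided.
- Drop the description of 62 per group as an addition for reliability. State its power for the dose comparison: 80.3% with no loss and about 71% with 20% loss.
- Say explicitly that these figures apply only to propofol dose compared between equal-sized dream and no-dream groups, and do not show power for comparing dreaming between the randomised BIS groups.

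Use one loss expectation in the Sample size section and item 20c: either keep the 20% in both, or say that little loss is expected and treat the 20% as an allowance that 124 patients do not cover.

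The trial need not be enlarged; Trial status reports recruitment as finished. The cost is a few sentences of wording and an honest power statement. Allocation, conduct and analysis do not change.

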### Observation indicators {12}

#### General data

The following patient data were collected from the anesthetic records: age, gender, height, weight, body mass index (BMI), American Society of Anesthesiologists physical status (ASA), duration of falling asleep, duration of surgery, duration of anesthesia, duration of recovery to consciousness (time between withdrawal of drugs and orientation of patients to time, place, and person), and drugs used for anesthetic management. The Hospital Anxiety and Depression Scale (HADS) is a self-report questionnaire used to assess the anxiety and depression status of participants during the perioperative period (Fig. 2). We used the Japanese version of HADS in this study. HADS consists of two subscales: anxiety (HADS-A) and depression (HADS-D). Each score consists of 7 questions, ranging from 0 to 3 (each score is 0–21), depending on the probability of the psychological problem described. Patients with a score of 11 or higher can be classified as possibly significant [13, 14]. We evaluated HADS score of patients the day before surgery.

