## Discussion

Dreams are a remarkable experiment in psychology and neuroscience, conducted every night in every sleeping person. They show that the human brain, disconnected from the environment, can generate an entire world of conscious experiences by itself. The occurrence of dreams is also one of the common phenomena of anesthesia and sedation. The occurrence of dreams during general anesthesia has been reported in the literature. The dream after anesthesia refers to the patient’s experience after the induction of anesthesia to the beginning of the waking phase. Domestic scholars have conducted research on the effects of short-town intravenous anesthesia and specific anesthetics on dreams of adult receiving surgery, which found that the incidence of adult dreams is about 18% ~ 49.7% [19, 20]. Among them, different anesthesia drugs, operation site, operation time, and so on are all the influential factors leading to the occurrence of dreams. Previous hypothesis also thought that dreaming occurs intraoperatively and is related to light or inadequate anesthesia [21, 22]. In order to verify this previous hypothesis, we designed a randomized, observer- and patient-blinded, controlled clinical trial, which compared the effects of different maintenance doses of propofol on patients’ dreams and analyzed the related factors affecting dreams. A recent study has shown that depression and anxiety assessed by Beck anxiety/depression inventory can predict a negative dream during natural sleep [23]. Similarly, we assessed preoperative anxiety level to see if patients with different preoperative anxiety states were associated with different dreams generated during anesthesia. In our trial, the subjective outcomes including HADS, Ramsay scale, modified Brice questionnaire, and awareness classification will be assessed. In this way, the effect of different dose of propofol maintained during the surgery on the incidence of dreaming of patients will be evaluated from multiple perspectives.

Our study has some limitations. First, since all the patients were hospitalized, we only scored the preoperative anxiety during the perioperative period but did not evaluate the daily long-term psychological base state and the degree of dreaming under natural sleep. Second, the study was part of a single-center survey, multicenter survey still need to be studied.

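### The plan allows continuous variables to be categorised without a rule, beside a logistic model that could take them as they are; the predictor analysis loses information, how much depending on the cuts

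*Protocol article*

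**What the plan says.** All references are to the protocol article. Under Statistical analysis (in the text below Sample size) the plan states "Logistic regression was used to determine predictors of dreaming and correlation with dream quality", and the next sentence is "Categorical variables were created from continuous variables in applicable cases". The paragraph closes with one significance threshold for everything: "A *P* value of less than 0.05 was considered statistically significant".

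Under General data, each HADS subscale runs from 0 to 21 and is scored the day before surgery. The section gives one threshold, attributed to published references: "Patients with a score of 11 or higher can be classified as possibly significant". Age, height, weight, BMI and several durations are collected as well.

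The predictor analysis is a stated aim. The Discussion says that the trial compared propofol maintenance doses and "analyzed the related factors affecting dreams", and that anxiety was assessed before surgery to see whether it goes with different dreams. The Conclusion lists the analysis of associated factors after the comparison of dream proportions between the arms.

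**The concern.** The sentence is a choice already made, not a detail left for later. Some continuous variables will become categories, and no reason is given. Age, BMI and HADS scores need no grouping to enter a logistic model, and grouping them treats patients within a category as identical.

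Two separate things are at stake. The first is precision: with 124 patients, a real association between, say, preoperative anxiety and dreaming becomes harder to detect. The second is validity, and it is conditional: the wording leaves open where the cuts fall and when they are set. If they were set by looking at which cut separates dreamers from non-dreamers, the 0.05 threshold would no longer mean 5%.

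**Working it through.** The documents give no figure for this loss, so there is none to reproduce.

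**Inputs.** From the documents: N = 124; dream incidence 18% to 49.7% (Discussion), so 124 × 0.18 = 22.3 to 124 × 0.497 = 61.6 dreamers; threshold 0.05. Assumed: a normally distributed predictor acting linearly on the log-odds; a 30% dream rate as a middle value.

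**1. Two-group split.** With a proportion q above the cut z, efficiency relative to the continuous term is φ(z)² / [q(1 − q)].

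| Share above cut | φ(z) | Efficiency | Loss |
|---|---|---|---|
| 50% | 0.3989 | 0.1592 / 0.25 = 0.637 | 36% |
| 20% | 0.2800 | 0.0784 / 0.16 = 0.490 | 51% |
| 10% | 0.1755 | 0.0308 / 0.09 = 0.342 | 66% |

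At the median this equals working with 124 × 0.637 = 79 patients, about 45 fewer.

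**2. More groups.** For k equal groups, the information kept is the mean of the squared group means of a standard normal variable. For k = 3 the group means are −1.091, 0 and 1.091, so 2 × 1.190 / 3 = 0.793 is kept and 21% lost. For k = 4 and 5 the losses are 14% and 10%. Entered as separate categories, such a variable needs k − 1 coefficients instead of one.

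**3. Effect on power.** A test with 80% power has noncentrality 1.960 + 0.842 = 2.802.
- Median split: Φ(2.802 × √0.637 − 1.960) = Φ(0.275) = 0.61.
- 10/90 split: Φ(2.802 × √0.342 − 1.960) = Φ(−0.322) = 0.37.

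A logistic simulation (n = 124; dream rates 18%, 30% and 49.7%; effects giving the continuous term 82–83% power) gave 0.62–0.66 for the median split and 0.38–0.54 for a cut with 10% above. The formula is therefore close for the median split, and for the extreme cut it overstates the loss when dreaming is uncommon.

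**4. Type I error.** Null simulation, n = 124, the same three dream rates, 10,000 runs per setting, nominal 5%:

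| How the cut is set | Type I error |
|---|---|
| Median, fixed in advance | 0.045–0.062 |
| Best of three quartile cuts | 0.12–0.14 |
| Best of all cuts, central 50% of the range | 0.28 |
| Best of all cuts, central 80% of the range | 0.40–0.43 |

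**5. The one stated cut.** HADS 11 is fixed in advance, so it belongs with the first row of step 4. Its information loss depends on how many patients score 11 or more, which the article does not give. If 10% to 50% do, the loss is 66% to 36% under normality; HADS scores are integers and may be skewed, so this is approximate.

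**The case against.** The strongest reply is that the sentence says little. It speaks of categories, not of two groups, is not expressly limited to the logistic model, and could cover descriptive tables or the chi-square comparisons. Variable lists and cut-points commonly go to a statistical analysis plan, and their absence from an article is no fault. The one cut given comes from published references, and a recognised threshold is a reasonable way to define anxiety states.

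Much of that stands, and it rules out several stronger readings:

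- *That a third to two thirds of the information will be lost.* That range needs a two-group split between the median and the 10/90 point. Three to five groups lose far less.
- *That the predictor P values are too small.* This needs cut-points picked from the data, which the article neither states nor excludes.
- *That age, BMI, HADS, durations and propofol dose will all be cut.* No variable is named.
- *That propofol dose, Ramsay score or satisfaction will be entered beside trial arm and absorb part of its effect.* No such model is described.
- *That the model is overfitted.* No parameter count is given to set against the 22 to 62 expected dreamers.

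What does not stand is that nothing remains. Categorising is a stated choice, it directly follows the logistic regression sentence, and a more precise alternative uses data already collected.

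**Conclusion.** The point holds as a criticism of a stated analysis choice with a conditional cost. The loss figures assume a normal, linearly acting predictor; the false-positive figures apply only to data-chosen cuts. The consequence is confined to the predictor analysis, which is a stated aim but not the randomised contrast: the unadjusted chi-square or Fisher comparison of dream rates between the low and high BIS arms is untouched. It is worth correcting because the better method costs almost nothing, not because a wrong result is shown to follow.

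**What to change.** Replace the sentence with: *Continuous predictors are entered as continuous terms; any categorised version uses cut-points fixed before group allocation is opened (HADS 11 or higher as a supplementary analysis).* It is safer to add that cut-points are fixed before any predictor is tabulated against dreaming, because a cut can be tuned to the outcome without knowing the allocation.

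Report the BIS-arm effect on dreaming adjusted for a few prespecified baseline covariates, for example age, sex and HADS-A, beside the chi-square result. Keep any model with post-randomisation variables, such as propofol dose, separate and labelled exploratory. That last step is a safeguard, since propofol is adjusted to reach the BIS target (Standardized anesthesia).

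The cost is wording; no new data are needed. The Trial status section reports data collection still in progress, and Randomization places the opening of allocation at data analysis, so on the article's account the change could precede it. Per-unit odds ratios are slightly less familiar to readers than categories, and the covariate-adjusted odds ratio for arm need not equal the unadjusted one even with balanced arms, so the report should label each.

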## Introduction

Dreaming is a familiar and mysterious mode of cognitive function, and we involuntarily return to this mode every night. Dreaming during sleep is defined as “any type of cognitive activity that occurs during sleep” and is “a subjective experience that can only be obtained through the dreamer's memories after waking up.” Despite more than a century of scientific exploration, dreams continue to arouse the interest of sleep scientists, but they are still not fully understood [1, 2]. Moreover, its rigorous scientific exploration is a recent development, dating back to the discovery of rapid eye movement (REM) sleep in the 1950s. When this stage of sleep was first described in humans, researchers quickly noticed that people who awakened from REM sleep often reported dreaming (in 74% of cases, only 17% of non-REM [NREM] sleep). Therefore, dreaming is equivalent to rapid eye movement sleep, and this concept seems to be consistent with the electrophysiological characteristics of this sleep stage: closing the eyeballs under the eyelids, as if the sleeper is watching an animated scene [3, 4]. General anesthesia causes a drug-induced state of unconsciousness and is a non-physiological process that is similar to natural sleep. Its purpose is to create a state of sensory deprivation wherein patients are unresponsive to stimuli and thus leads to explicit amnesia [5]. Dreaming is also a common, long-lasting, and fascinating part of the anesthesia experience, but its cause and timing are still elusive. Patients usually report that they dreamed during anesthesia, but the actual time of dreaming during anesthesia is unknown. Dreaming during anesthesia can be defined as “any experience (excluding awareness) that a patient is able to recall and which he or she thinks occurred between induction of anaesthesia and the first moment of consciousness after anaesthesia” [6]. Patients receiving propofol for general anesthesia often report a higher incidence of dreaming compared with patients maintained with volatile anesthetics [7]. One explanation is that propofol and volatile anesthetics have different pharmacological effects in the central nervous system [8, 9]. Another explanation is that propofol can wake up from anesthesia faster than the volatile anesthetics, allowing patients to report their dreams before they are forgotten [10]. Why is the investigation of dreams during anesthesia important? Dreaming is one of the most common side effects of anesthesia, but it is still puzzling and requires explanation [7, 11]. Dreaming can sometimes make patients feel distressed and may reduce satisfaction with care [12]. Some patients who report dreaming worry that their anesthetic is insufficient; their experience is actually consciousness. At present, there is a hypothesis that dreaming occurs intraoperatively and is related to light or inadequate anesthesia; thus, in order to further verify the hypothesis, we choose elective surgery under general anesthesia to observe whether the generation of dreams is related to the dose of general anesthetics maintenance.

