## Conclusion

In conclusion, the results of our trial are expected to demonstrate the proportion of patients in the HBIS group who had dreams during the surgery vs that of patients in the LBIS group and whether there are patient-reported awareness during anesthesia. Through all the patients who reported dreaming during the surgery, we are aimed to explore the proportion of those who reported having pleasant dreams in the LBIS group vs that of patients in the HBIS group, to further compare whether there is a difference in the dosage of propofol between the two groups, and to analyze the factors associated with different postoperative dream generation. In summary, according to the study results, we hope to provide a basis for good perioperative experience and better postoperative recovery of patients in clinical practice.

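### No comparison is named as primary, and the sample size is tied to a non-randomised dose contrast instead of to dreaming by BIS arm

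*Protocol article*

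**What the plan says.** The Introduction gives one purpose. There is a hypothesis that dreaming arises from light or inadequate anaesthesia, and "in order to further verify the hypothesis, we choose elective surgery under general anesthesia". Patients are randomised 1:1 to BIS 40–50 (LBIS) or BIS 50–60 (HBIS), 62 per arm.

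The Observation indicators section lists what is collected: HADS, haemodynamics, total propofol, Ramsay score, satisfaction, the modified Brice questionnaire and the awareness classification. It ranks none of them.

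The Conclusion says that the results should show "the proportion of patients in the HBIS group who had dreams during the surgery vs that of patients in the LBIS group", then awareness, then pleasant dreams by arm among dreamers, then "to further compare whether there is a difference in the dosage of propofol between the two groups", and then factors associated with dreaming.

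The Sample size section rests on a different contrast, taken from a previous study: "the total dose of propofol in the dream group was 337 ± 161 mg", against 259 ± 145 mg in those without dreams. Alpha of 0.05 and power of 0.8 are attached to a two-sample t test of that difference.

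The same section adds that "Logistic regression was used to determine predictors of dreaming and correlation with dream quality", and ends with the rule that a P "value of less than 0.05 was considered statistically significant". No hierarchy, division of alpha or exploratory label accompanies the rule.

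**The concern.** A trial that sets out to verify one hypothesis needs one comparison whose result settles it. Here two candidates compete. One is randomised and matches the title. The other is observational, and it is the only one to which alpha and power are attached.

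The two need not agree. The hypothesis predicts more dreaming in HBIS, the lighter arm, where less propofol would be expected. The sizing figures have dreamers receiving 78 mg more propofol than non-dreamers. If a higher total dose is read as deeper anaesthesia, a trial that reproduced the sizing effect would speak against the hypothesis it was sized to examine.

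With every test judged at the same threshold and none given precedence, a null result for dreaming by arm could be overshadowed in the report by a dose difference, a predictor from the logistic model or a difference in dream quality. The protection that randomisation gives to the main question would then be lost.

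**Working it through.** **1. The plan's own figure, and what it measures.** Inputs from Sample size: means 337 and 259 mg, SDs 161 and 145, alpha 0.05, power 0.8, 20% withdrawal. Two-sided testing is given in the Statistical analysis section.

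- Difference: 337 − 259 = 78 mg.
- Common variance: (161² + 145²)/2 = (25,921 + 21,025)/2 = 23,473, so SD = 153.2.
- n per group = 2 × (1.96 + 0.8416)² × 23,473 / 78² = 60.6, so 61 (62 with the t distribution).
- With 20% withdrawal: 61/0.8 = 76.3, so 77.

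The stated 56 per group is not reproduced. That is a separate matter. What counts here is that the groups in this calculation are dreamers and non-dreamers, whose numbers no allocation controls. They are not the 62 and 62 patients randomised.

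**2. The two candidates side by side.**

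| | Dreaming by arm | Dose by dream status |
|---|---|---|
| Where it appears | Title; first item in Conclusion | Sample size |
| Outcome | Binary (dream or no dream) | Continuous (total mg) |
| Groups | Randomised | Formed after the outcome is known |
| Alpha and power attached | No | Yes |
| Direction | Hypothesis: more dreams at higher BIS | Sizing figures: more propofol in dreamers |

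**3. Power for the randomised comparison.** The article gives no dream rate by arm. The Discussion quotes an overall range of 18% to 49.7%, so the pairs below are assumptions within it. With n = 62 per arm, two-sided 0.05, and p̄ the mean of the two rates:

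power = Φ{ [|p₁ − p₂| − 1.96 √(2p̄(1 − p̄)/n)] / √[(p₁(1 − p₁) + p₂(1 − p₂))/n] }

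- 18% v 33%: 0.48
- 30% v 49.7%: 0.61
- 18% v 49.7%: 0.97

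So 62 per arm may be ample or inadequate for dreaming by arm, and the dose calculation cannot tell which.

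**4. Chance of at least one false positive among the dream-related contrasts.** For k independent two-sided tests at 0.05, the rate is 1 − 0.95^k.

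- k = 2 (dreaming by arm; dose by dream status): 1 − 0.95² = 0.0975.
- k = 3 (adding pleasant dreams by arm among dreamers): 1 − 0.95³ = 0.143.
- k = 3 with correlation 0.5 between the tests: 0.125.

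**5. Simulation of the three tests.** There were 4,000 runs at 62 per arm. Dreaming was unrelated to arm or dose, and 60% of dreams were pleasant (assumed). The tests were chi-squared for dreaming by arm, t for dose and Fisher's exact for pleasantness. At an assumed 30% dreaming, the separate rejection rates were 0.045, 0.050 and 0.033, and at least one test was significant in 0.12 of runs. A separate simulation at dreaming rates of 18%, 34% and 49.7% gave 0.112, 0.121 and 0.129. That one also assumed an 80 mg dose gap between arms with SD 150.

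**The case against.** The best reply is that the lead comparison is easy to identify. The title is about BIS level and dreaming, the Brice questionnaire is introduced to measure incidence, and the Conclusion puts dreaming by arm first and brings in dose only afterwards. On this view the defect is a missing label, and rules for multiplicity may sit in an analysis plan that is not shown. Much of that stands: dreaming by arm is the natural lead, and the lack of an adjustment would not be a finding by itself. But the sample size, where a primary comparison normally shows itself, points elsewhere. An unseen plan does not remove that conflict from the printed text.

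Other parts of the reply also stand:

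- Dose by dream status is not announced as a planned test. It appears as a sizing input and could enter the logistic model as a predictor. The dose comparison in the Conclusion most naturally means the two arms.
- Pleasantness among dreamers does not bear directly on whether light anaesthesia causes dreaming. With two contrasts, and counting only results in the hypothesised direction, the rate is 1 − 0.975² = 0.049. The matching figure for a single contrast is 0.025, so the rate still roughly doubles.
- Total milligrams can depend on operation length and body weight, so the sign of the dose contrast is not a clean measure of depth. The conflict in direction is therefore conditional.

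A reader might also take the remark in the Discussion that the effect "on the incidence of dreaming of patients will be evaluated from multiple perspectives" to mean that the deciding contrast will be picked once the data are seen. The text does not say so. The remark follows a list of instruments and concerns one outcome.

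**Conclusion.** The point holds in this form: the article names no deciding comparison, its own signals conflict, and the flat 0.05 rule does not settle which result answers the hypothesis. For the two or three contrasts that concern dreaming, the false-positive rate is about 0.10 to 0.14 under independence and about 0.12 in simulation, against a stated 0.05. The simulated value rests on assumed dream rates and an assumed share of pleasant dreams.

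A reader might infer a much larger error rate by counting everything recorded, including Ramsay score, satisfaction, recovery time, and blood pressure and heart rate at five times. The documents do not support that, because those measures do not bear on the hypothesis. A false-positive rate for the logistic predictors would need a number of predictors that the article does not give. A probability that dose differs by arm would need arm doses that it does not give either, and no passage offers such a difference as the test of dreaming. Nor do the documents show that the two candidate contrasts must come out opposed, only that they can.

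**What to change.** Before the allocation is opened for analysis, amend the statistical section along these lines:

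- *The primary outcome is the proportion of patients reporting a dream on the modified Brice questionnaire. The primary comparison is HBIS v LBIS by intention to treat, at two-sided alpha 0.05. It alone decides whether the hypothesis is supported.*
- *The sample size was derived from propofol dose by dream status and does not give the power for the primary comparison.*
- *Propofol dose by arm is reported as a check that the intervention separated the arms.*
- *Pleasant dreams, awareness, dose by dream status and the logistic predictors are secondary or exploratory.*

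The cost is a few sentences and an update through the route in Protocol amendments, with no new patients or data. Timing matters. Trial status reports recruitment finished and data collection in progress, and the randomisation section keeps the allocation closed until analysis. A primary comparison chosen after that would lose most of its value. The downside is that nominally significant secondary results can no longer be presented as confirming the hypothesis.
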